### Objectives {7}

#### Primary endpoints

The primary objective of this study is to analyze the safety and efficacy of The Prehab App before major surgical procedures. We hypothesize that the rate of postoperative morbidity can be reduced from 60 to 45%. The primary endpoint is the occurrence of any postoperative complication within 90 days after surgery according to the Clavien–Dindo classification (grades I–V).

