The software facilitates home-based, remote exercise sessions, which can occur outdoors in nature or indoors on a treadmill, indoor cycle, or indoor track, at any time of day. Patients have autonomy in selecting their exercise environment, including factors such as lighting, noise level, terrain, location, and timing, to suit their schedule and preferences.

The comparator group is using the Ready4Op App which gives information generally provided preoperatively.

After completing the Prehab program via the app as described above, upon return to the hospital and prior to surgery, a second risk assessment is conducted. Here, delta values are calculated, indicating improvements, a stable condition, or a decline in assessed points, serving as decision support for continuing with the operation or assigning alternative therapies.

Throughout the program, a safety check is initiated on both the physician and patient displays according to an algorithm derived from the software’s risk management. To track app or device failure, safety, and misuse scenarios, testing the app’s alarm settings will be conducted at the same time. A 24/7 emergency hotline connects patients to the treating hospital. Physicians can monitor the exercise data of each patient in their department to track progress, while individual patients can review their progress within the app.

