### Criteria for discontinuing or modifying allocated interventions {11b}

Patients can leave the study at any time for any reason if they wish to do so without any consequences.

In case too much data is missing (e.g., missing baseline or all of the follow-up patient-reported outcome measures (PROMs), study visits), the patient will be replaced by a new patient. Early termination or temporary suspension may be recommended exclusively by the DSMB or sponsor following DSMB recommendation in case of unexpected serious safety concerns, unacceptable adverse event patterns, major protocol violations compromising participant safety, or regulatory authority requests such as ethics committee or the BfArM.

Termination criteria: unexpected safety concerns such as a significant increase in frequency or severity of serious adverse events related to the intervention, an unacceptable benefit-risk ratio therefore indication of potential risks of the intervention outweighing its anticipated benefits, a regulatory or ethical requirement due to regulatory, ethical or legal concerns, major protocol violations or GCP violations that compromise participant safety, data integrity or scientific validity, insufficient recruitment or feasibility despite corrective measurements, rendering completion of the study within the planned timeframe scientifically or operationally unfeasible, poor intervention adherence that prevents meaningful evaluation of the primary endpoint despite corrective actions, data integrity concerns, funding or logistical concerns preventing continuation of the study.

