### Adverse event reporting and harms {22}

#### Adverse events

All adverse events (AEs), adverse device effects (ADEs), serious adverse events (SAEs), and serious adverse device effects (SADEs) occurring during the prehabilitation or subsequent follow-ups will be documented in the electronic case report form (eCRF). An AE is characterized as any undesirable sign, symptom, or disease temporally associated with the application of the device, without necessitating a causal relationship. If a potential causal relationship with the device is conceivable, the AE is classified as an ADE. For all AEs and ADEs, the duration, consequences, and assessment of their relationship to the device will be recorded. AEs or ADEs resulting in life-threatening illness, injury, extended hospitalization, permanent disability, necessitating medical or surgical intervention, or death will be designated as SAEs or SADEs. They will be promptly reported to the sponsor, legal representative, and manufacturer in accordance with the regulatory obligations of the Medical Device Regulation (MDR) and the Medical Device Law Implementation Act (MPDG). Appropriate follow-up actions will be undertaken as required.

The reporting of SAEs and device deficiencies will be carried out in accordance with the Regulation (EU) 2017/745 (MDR) from May 26, 2021, in conjunction with the Medical Device Law Implementing Act (“Medizinprodukterecht-Durchführungsgesetz,” MPDG) for all clinical investigations that must be applied for or notified to the federal higher authority (“Bundesoberbehörde”). For all reportable events according to Article 80 MDR or § 64 paragraph 1 MPDG which indicate an imminent risk of death, serious injury, or serious illness and that requires prompt remedial action for other patients/subjects, users, or other persons or a new finding to it: immediately, but not later than 2 calendar days after awareness by the sponsor of a new reportable event or of new information in relation with an already reported event. This includes events that are of a significant and unexpected nature such that they become alarming as a potential public health hazard. It also includes the possibility of multiple deaths occurring at short intervals.

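### The seriousness list for adverse events omits a new hospital admission and puts no limit on the intervention criterion, so an untreated admission from home is not an SAE while any treated surgical complication can be one

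*Protocol article*

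**What the plan says.** Under Adverse event reporting and harms {22}, the protocol article collects AEs, ADEs, SAEs and SADEs from the prehabilitation period through the later follow-ups. An AE is an undesirable event "temporally associated with the application of the device, without necessitating a causal relationship". It becomes an ADE if a causal link to the device is conceivable. For every AE and ADE, "the duration, consequences, and assessment of their relationship to the device will be recorded".

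Seriousness is then fixed by a list. It opens with life-threatening illness and injury and continues: "extended hospitalization, permanent disability, necessitating medical or surgical intervention, or death will be designated as SAEs or SADEs". Events in this class go promptly to the sponsor, the legal representative and the manufacturer. Reporting is tied to the MDR and MPDG. The quarterly summary takes in reportable SAEs and, in addition, SAEs that are part of the study endpoints.

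Four other places bear on this:
- Intervention description {11a}: "The software facilitates home-based, remote exercise sessions".
- Primary endpoints: any complication of Clavien–Dindo grade I to V within 90 days of surgery, with hypothesized rates of 60% and 45%.
- Statistical methods {20a}: SAE data are presented descriptively. Onset date and time, severity and possible causality are recorded.
- Criteria for discontinuing {11b}: termination may follow "unexpected safety concerns such as a significant increase in frequency or severity of serious adverse events related to the intervention".

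**The concern.** The device is used while the patient is at home, so during that time there is no hospital stay to extend. If *extended* is taken to mean simply *long*, a short admission still fails the criterion. A participant who becomes unwell in a session, is admitted, monitored and sent home untreated and uninjured meets no item on the list. That event therefore misses the prompt report that the serious class triggers.

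The intervention criterion errs in the other direction. It sets no severity and no purpose, and an AE needs no causal link to the device. A postoperative complication treated with a single drug can therefore be an SAE. Low-grade complications are part of the primary endpoint, so an undivided SAE total would partly restate the efficacy result. Safety is part of the stated primary objective and the DSMB receives quarterly safety reports, so the classification should separate events of the exercise phase from the expected consequences of surgery.

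**Working it through.** **Step 1: what the list catches during the exercise phase.**

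| Event at home | Criterion met | Class |
|---|---|---|
| Admission with any treatment | intervention | SAE/SADE |
| Admission with an injury | injury | SAE/SADE |
| Admission for observation or diagnostics only, nothing else met | none | AE/ADE only |

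The gap is the third row. After discharge, an untreated readmission falls in the same row.

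**Step 2: the plan's own figures.** The safety section states no number. The base for the SAE load is the sample size. For 60% against 45%, two-sided 0.05 and 80% power, without continuity correction:

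n = [1.960·√(2·0.525·0.475) + 0.842·√(0.60·0.40 + 0.45·0.55)]² / 0.15² = 172.8, rounded up to 173 per arm.

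This reproduces the stated 173. The stated 191 is 173 × 1.10 = 190.3, rounded up. Dividing by 0.90 would give 193, a difference that does not matter here.

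**Step 3: patients with a complication.** 191 × 0.60 + 191 × 0.45 = 114.6 + 86.0 = 200.6, or 52.5% of 382.

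**Step 4: patients who become SAE patients through the intervention criterion alone.** Let f be the share of patients with a complication who receive any medical or surgical treatment. The documents do not give f, so a range is shown. SAE patients = f × 200.6.

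| f (assumed) | SAE patients | Share of 382 |
|---|---|---|
| 0.25 | 50 | 13% |
| 0.50 | 100 | 26% |
| 0.75 | 150 | 39% |
| 1.00 | 201 | 53% |

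With 173 per arm, the base is 173 × (0.60 + 0.45) = 181.7 and the range is about 45 to 182.

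**Step 5: what pooling would do (illustration only).** Suppose true SAE rates in the exercise phase were 5% with the app and 1% without. Both rates are assumptions. Compared alone, with 191 per arm, power is about 63%. Pooled with an equal surgical background, the rates are 1 − (1 − 0.60f)(1 − 0.05) and 1 − (1 − 0.60f)(1 − 0.01):
- f = 0.25: 19.3% against 15.9%, power about 14%.
- f = 1: 62.0% against 60.4%, power about 5%.

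If complications instead fall to 45% with the app, as hypothesized, the pooled difference (app minus control) runs from about −0.2 points at f = 0.25 to −12.6 points at f = 1. An excess in the exercise phase would then not show in the pooled total.

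**The case against.** The strongest reply is that the two halves limit each other. If any treatment makes an event serious, then nearly every admission from home already qualifies, and injury is listed without a qualifier too. This stands, and it confines the gap to admissions without treatment or injury. A reader might infer that the typical serious event of a home exercise programme is lost. The documents do not support that. They give no distribution of such events, and an untreated admission is still recorded as an AE or ADE with its consequences and device relationship. Weekly visits with a safety audit and a 24/7 hotline are planned, and readmission is a separate secondary outcome. What is lost is the serious label and the prompt report.

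A reader might also infer that the termination rule is compromised, or that a device signal is hidden in either direction. The rule in Criteria for discontinuing {11b} concerns SAEs related to the intervention, SADEs are a separate class, and causality is recorded. Dilution arises only if SAEs are pooled, and the article does not say that decisions will rest on a pooled count. How tables are split is commonly left to an analysis plan, so the absence of a split is not itself a fault.

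The size is also open to challenge. The treated share is assumed. About 115 of the 201 patients are controls, and because AEs are tied in time to application of the device, counting their complications as SAEs is an inference. With the intervention arm alone the range is 0.25 × 86.0 to 86.0, about 21 to 86 patients.

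Finally, this is a condensed article and the full clinical investigation plan may carry a complete definition. That is possible. But the article states a specific list, and a general reference to the MDR and MPDG for reporting does not correct that list as written. Separate SADEs do not close the first gap either: an event that meets no seriousness criterion cannot be a SADE.

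**Conclusion.** The concern holds in a limited form. As written, the list leaves an untreated, uninjured new admission or readmission outside the SAE/SADE class, and it lets any treated postoperative complication in. The first effect cannot be sized from the documents and is confined to prompt reporting, because the event is still recorded. The second could make about 50 to 201 of 382 patients SAE patients, given the protocol's 60% and 45% rates, both arms counted, and an assumed treated share of 25 to 100%. It affects the undivided SAE total in the descriptive and quarterly summaries and leaves the termination criterion for intervention-related SAEs untouched. The power figures only illustrate what pooling would do under assumed rates; they do not show that a signal will be missed. The wording should be corrected, but this does not threaten the primary analysis.

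**What to change.** In the Adverse events section:
- Name unplanned new hospitalization as well as prolongation of an existing stay, with the planned admission for the index surgery excepted.
- Qualify the intervention criterion by purpose or severity, in line with the regulation the protocol cites.
- Tabulate SAEs separately for randomisation to surgery and for surgery to day 90, by arm, using the onset dates already recorded. Endpoint complications then stay visible without being mixed with exercise-phase events.
- If the full investigation plan already has such a definition, bring the article's wording into line with it.

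The cost is a revised definition and training text and, if needed, one eCRF field. SAE counts would shift slightly: probably fewer from surgery and a few more from the exercise phase. Recruitment started in December 2025, so events already entered should be checked against the revised list; the recorded consequences should help with this.

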### Frequency and plans for auditing trial conduct {23}

Details and amount of monitoring are in general defined by the risk category according to the Human Research Act and confirmed by the SCTO-“Monitoring Risk Analysis.” Oversight of the trial conduct is provided through regular monitoring according to the Good Clinical Practice and ISO 14155 standards. Further criteria (such as the experience on-site, the use of a validated database, and function as the coordinating site) could increase or decrease the extent of monitoring for a clinical investigation. For the LUMOS trial, a risk category of low to medium risk was defined. Every site needs a site initiation visit that includes structured training in documents. The training can be done remotely. One hundred percent of informed consent needs to be checked. The first visit should take place after 1–2 patients at sites that plan to include less than 20 patients and after 5 patients at larger sites. A random list of approximately 80 patients (1 for each 5 randomized at each center) will define the patients that require monitoring of key data. This accounts for >20% of all patients that were included. In case there are repeated problematic findings at a site, the sponsor can increase the number of monitoring of key data of the clinical investigation to 50%. There shall be 1 visit per year at unproblematic sites or sites with less than 20 patients and 2 visits per year at problematic sites or with more than 20 patients. Queries by the monitor will be done via eCRF structure. Each monitoring visit will include a monitoring report with a response by the project management group addressing each finding and query by the monitor. Monitoring is done approximately every month, depending on recruitment numbers. A close-out visit will be performed at each site. This can be done remotely. For more information, the monitoring plan can be consulted. The Project Management Group is responsible for daily trial conduct and meets weekly. Internal auditing according to the standard operating procedure of the central study coordination will be conducted twice a year. All CAPAs will be written down. Vendor audits and external audits will take place at least once a year. Auditing can also take place by national or international health authorities.

### Plans for communicating important protocol amendments to relevant parties (e.g., trial participants, ethical committees) {25}

In case of the necessity of an amendment, we will adhere to the CAPA SOP in the DIN ISO14155 compliant clinical trials management. All changes will be documented in the document history. We use versions. For a significant amendment, we will go from, e.g., version 1 to 2 or 3, etc. For a minor amendment, we will go from, e.g., version 1 to version 1.1 or 1.2, etc. Reasons for an amendment can be recommendations by the DSMB, requests by authorities, or changes can be necessary because of vigilance signals or internal/external audits that may occur during the trial. The CAPA process will define if it is a significant major or minor amendment. The clinical trial will be continued with the old protocol in case of a minor protocol amendment until the new protocol version has been approved or the clinical trial will be set on hold in case there is a major safety-relevant amendment to the CIP. All substantial amendments will be notified to the competent authority. If amendments affect participants in any way, they are informed about the changes. If needed, additional consent will be requested and registered. Also, online trial registries will be updated accordingly. All substantial protocol amendments will first be reviewed and approved by the sponsor and relevant authorities/ethics committees, after which participating centers will be informed by the principal investigator. Updated protocol versions will be filed in the Investigator Site File. Protocol deviations will be documented in a breach form, and trial registry entries will be updated where applicable.

### Patient and public involvement

Formal patient and public involvement in the protocol design was limited, but patient-centered aspects of the intervention were informed by prior usability and feasibility work with the app and by the inclusion of patient-reported outcomes. Furthermore, there has been a dedicated peer analysis of all stakeholders that were published elsewhere as well as a usability trial in potential patients and patients as well as other stakeholders that showed excellent usability of our solution that is now tested in its final intended use [23].

### Dissemination plans {31a}

The study protocol and the results of the study will be reported in scientific journals. The results of this research will be disclosed completely in international peer-reviewed journals. Both positive and negative results will be reported. The publication policy should cover authorship, acknowledgments, and review procedures for scientific publications. Participants will be informed about study results upon request.

## Discussion

Despite advancements in surgical care, mortality rates among surgical patients remain substantial, accounting for 8% of all hospital deaths [2]. While improvements in patient selection, perioperative protocols such as ERAS, surgical techniques, and multimodal treatment strategies have been made, there is still a pressing need for further enhancement [24]. The perioperative phase, including the period before elective surgery or during neoadjuvant therapy, presents an opportunity to optimize patient outcomes [25]. Identifying and addressing preoperative modifiable risk factors is crucial in this regard, with robust risk scoring systems being integral tools in risk assessment. The risk calculator integrated into The Prehab App utilizes scientifically validated risk scoring systems to tailor prehabilitation strategies for individual patients [26–29].

While some studies have demonstrated improvements in postoperative outcomes with prehabilitation, there remains considerable heterogeneity in study designs, limiting comparability and complicating the implementation of prehabilitation programs in clinical practice [12, 30]. Additionally, the impact of prehabilitation on mortality outcomes remains debated, with conflicting findings across studies [31, 32].

Prior studies as the “Protego Maxima” trial have underscored the potential of digital tools, such as “The Prehab App,” in risk screening and preoperative optimization. Evidence-based tools embedded within the app have shown promising correlations with short-term surgical outcomes, enhancing risk prediction and informing prehabilitation strategies [29].

The present study seeks to address these challenges by evaluating the effectiveness of a digital prehabilitation program and by developing a safe and valid medical device for reducing perioperative morbidity and mortality. In an era marked by pandemics, fast lifestyles, and strained healthcare systems, the need for remote, patient-centered interventions is paramount. The digital nature of the program allows for flexibility in usage, empowering patients to engage in prehabilitation from the comfort of their homes. The incorporation of objective assessments alongside patient-reported outcomes reflects the growing emphasis on holistic patient care in research.

Despite the promise of prehabilitation, divergent study outcomes underscore the need for further investigation and validation. The current trial aims to fill this gap by rigorously evaluating a digital individual prehabilitation program’s efficacy and by offering high-quality data by considering multiple surgical departments and multicentric high-volume centers. In the context of major surgical procedures, high-quality and meaningful data equate to mitigated harm resulting in enhanced quality of care. A key indicator of this is a reduction in 90-day postoperative morbidity among surgical patients. Analysis of postoperative days spent in normal wards, Intermediate Care Units (IMC), and Intensive Care Units (ICU) may provide insights into the severity of postoperative illness, with potential implications for long-term outcomes.

Digital healthcare applications offer a promising avenue for home-based interventions, enhancing patient engagement and accessibility. However, the availability of validated prehabilitation apps remains limited, highlighting the need for continued development and validation in this field.

### Limitations

There are some limitations to be considered. First, prehabilitation as understood in this study with the focus on bodily training excludes patients before cardiac surgery as well as trauma surgery patients. We do include all other surgical patients in this study, though. Furthermore, complication rates may vary across centers and surgical categories due to differences in surgical case mix and perioperative care pathways. Although the sample size calculation was based on previously published complication rates, potential center-related heterogeneity may influence the observed effect size. This will be addressed analytically by adjusting for center effects in the statistical models. Second, the follow-up period after surgery is relatively short (1 year) and long-term efficacy remains to be investigated. There might occur performance bias through different perioperative care and detection bias for subjective outcomes, but this should be negligible via training of study members and standard operating procedures. Lastly, only patients in possession of a smartphone can participate in this trial. These days, non-possession should be a rare occurrence.

